## Supplementary Results

### FIGURES

**Figure S1. Progression-free survival as assessed by investigator review (intention-to-treat population).**

Panel A shows the Kaplan–Meier curves for progression-free survival as assessed per RECIST 1.1, and Panel B shows the Kaplan–Meier curves for progression-free survival as assessed per iRECIST. Progression-free survival was estimated with the Kaplan–Meier method and compared between treatment groups using the stratified log-rank test. Hazard ratios and associated 95% two-sided confidence intervals were estimated by a Cox proportional hazards model. Stratification factors included Eastern Cooperative Oncology Group performance status, brain metastases, and liver metastases. *P* values are two-sided. Tick marks indicate censored data. EC=Etoposide/carboplatin.

#### A Progression-free Survival per Investigators per RECIST 1.1

[figure not shown]

#### B Progression-free Survival per Investigators per iRECIST

[figure not shown]

**Figure S2. Duration of response as assessed by blinded independent central review and investigator review (intention-to-treat population).**

Panel A shows the Kaplan–Meier curves for duration of response in patients who had a response assessed by blinded independent central review, and Panel B shows the Kaplan–Meier curves for duration of response in patients who had a response assessed by investigator review. This analysis included only patients who had an objective response as per RECIST 1.1. Duration of response was estimated with the Kaplan–Meier method and compared between treatment groups using the stratified log-rank test. Stratification factors included Eastern Cooperative Oncology Group performance status, brain metastases, and liver metastases. Hazard ratios and associated 95% two-sided confidence intervals were estimated by a Cox proportional hazards model. *P* values are two-sided. Tick marks indicate censored data. EC=Etoposide/carboplatin.

**A Duration Response per Independent Review Committee**

[figure not shown]

**B Duration Response per Investigators**

[figure not shown]

**Figure S3. Treatment procedure.**

EC=Etoposide/carboplatin; CR=complete response; PR=partial response; SD=stable disease; PD=progressive disease; AUC=area under the curve.

[figure not shown]

**Figure S4. Fixed-sequence test for multiple testing between treatment groups.**

A fixed-sequence test was used for multiple testing between treatment groups. Testing begins with the first hypothesis, H1, and each test is carried out without a multiplicity adjustment, provided that significant results are observed in all preceding tests. The fixed-sequence procedure controls the family-wise error rate because, for each hypothesis, testing is conditional upon rejecting all hypotheses earlier in the sequence.  $P_1$ =the one-side  $P$  value in the interim analysis;  $P_2$ =the one-side  $P$  value in the final analysis. A two-sided test with a significance level of  $\alpha=0.05$  was used for secondary efficacy endpoints and safety analysis. Two-sided  $P\leq 0.05$  was considered statistically significant with a 95% CI.

OS=overall survival; PFS=progression-free survival.

[figure not shown]

## TABLES

**Table S1. Tumor response as assessed by investigator review using RECIST 1.1.**

|                                 | Benmelstobart+Anlotinib+EC
group (N=246) | Anlotinib+EC
group (N=245) | EC alone group
(N=247) |
|---------------------------------|---------------------------------------------|-------------------------------|---------------------------|
| Objective confirmed response    |                                             |                               |                           |
| No. of patients                 | 188 (76.4)                                  | 187 (76.3)                    | 145 (58.7)                |
| 95% CI                          | 70.6-81.6                                   | 70.5-81.5                     | 52.3-64.9                 |
| P value                  | <0.0001                                     | <0.0001                       | Reference                 |
| Best objective response-no. (%) |                                             |                               |                           |
| CR                              | 1 (0.4)                                     | 1 (0.4)                       | 0                         |
| PR                              | 187 (76.0)                                  | 186 (75.9)                    | 145 (58.7)                |
| SD                              | 32 (13.0)                                   | 36 (14.7)                     | 64 (25.9)                 |
| PD                              | 12 (4.9)                                    | 7 (2.9)                       | 23 (9.3)                  |
| NE*                             | 14 (5.7)                                    | 15 (6.1)                      | 15 (6.1)                  |

Differences in response rate between the treatment groups were assessed with the stratified Cochran-Mantel-Haenszel test. *P* values are two-sided.

\* The best overall response could not be evaluated for patients who had no baseline or no postbaseline tumor assessments, and at least one lesion that could not be evaluated.

No.=number; CI, confidence interval; CR=complete response; PR=partial response; SD=stable disease; PD=progressive disease; NE=Not evaluated; EC=Etoposide/carboplatin.

**Table S2. Tumor response as assessed by investigator review using iRECIST.**

|                                 | Benmelstobart+Anlotinib+EC
group (N=246) | Anlotinib+EC
group (N=245) | EC alone group
(N=247) |
|---------------------------------|---------------------------------------------|-------------------------------|---------------------------|
| Objective response              |                                             |                               |                           |
| No. of patients                 | 157 (63.8)                                  | 139 (56.7)                    | 112 (45.3)                |
| 95% CI                          | 57.5-69.8                                   | 50.3-63.0                     | 39.0-51.8                 |
| P value                  | <0.0001                                     | 0.0114                        | Reference                 |
| Best objective response-no. (%) |                                             |                               |                           |
| CR/iCR                          | 1 (0.4)                                     | 0                             | 0                         |
| PR/iPR                          | 156 (63.4)                                  | 139 (56.7)                    | 112 (45.3)                |
| SD/iSD                          | 27 (11.0)                                   | 29 (11.8)                     | 54 (21.9)                 |
| PD                              | 5 (2.03)                                    | 3 (1.2)                       | 12 (4.9)                  |
| iUPD                            | 14 (5.7)                                    | 13 (5.3)                      | 8 (3.2)                   |
| iCPD                            | 29 (11.8)                                   | 46 (18.8)                     | 46 (18.6)                 |
| NE*                             | 14 (5.7)                                    | 15 (6.1)                      | 15 (6.1)                  |

Differences in response rate between the treatment groups were assessed with the stratified Cochran-Mantel-Haenszel test. *P* values are two-sided.

\* The best overall response could not be evaluated for patients who had no baseline or no postbaseline tumor assessments, and at least one lesion that could not be evaluated.

No.=number; CI, confidence interval; CR=complete response; iCR=immune complete response; PR=partial response; iPR=immune partial response; SD= stable disease; iSD=immune stable disease; PD=progressive disease; iUPD=immune unconfirmed progressive disease; iCPD=immune confirmed progressive disease; EC=Etoposide/carboplatin.

**Table S3. Safety summary.**

|                                                                               | Benmelstobart+Anlotinib+EC
group (N=246) |                | Anlotinib+EC group
(N=244) |                | EC alone group
(N=246) |                |
|-------------------------------------------------------------------------------|---------------------------------------------|----------------|-------------------------------|----------------|---------------------------|----------------|
|                                                                               | Any grade                                   | Grade $\geq 3$ | Any grade                     | Grade $\geq 3$ | Any grade                 | Grade $\geq 3$ |
| Any TEAEs                                                              | 246 (100.0)                                 | 232 (94.3)     | 244 (100.0)                   | 234 (95.9)     | 246 (100.0)               | 219 (89.0)     |
| TEAEs leading to any dose reduction or interruption                           | 180 (73.2)                                  | 137 (55.7)     | 178 (73.0)                    | 142 (58.2)     | 136 (55.3)                | 108 (43.9)     |
| TEAEs leading to any discontinuation                                          | 49 (19.9)                                   | 37 (15.0)      | 37 (15.2)                     | 26 (10.7)      | 26 (10.6)                 | 16 (6.5)       |
| TEAEs leading to death                                                        | 26 (10.6)                                   | 26 (10.6)      | 15 (6.2)                      | 15 (6.2)       | 17 (6.9)                  | 17 (6.9)       |
| Any TRAEs                                                              | 246 (100.0)                                 | 229 (93.1)     | 243 (99.6)                    | 230 (94.3)     | 245 (99.6)                | 214 (87.0)     |
| TRAEs leading to any dose reduction or interruption                           | 175 (71.1)                                  | 135 (54.9)     | 176 (72.1)                    | 140 (57.4)     | 128 (52.0)                | 103 (41.9)     |
| Benmelstobart/anlotinib-related AEs leading to dose reduction or interruption | 124 (50.4)                                  | 83 (33.7)      | 116 (47.5)                    | 79 (32.4)      | 57 (23.2)                 | 39 (15.9)      |
| TRAEs leading to benmelstobart/placebo interruption                           | 124 (50.4)                                  | 87 (35.4)      | 113 (46.3)                    | 80 (32.8)      | 82 (33.3)                 | 55 (22.4)      |
| TRAEs leading to anlotinib/placebo dose reduction or interruption             | 151 (61.4)                                  | 108 (43.9)     | 149 (61.1)                    | 109 (44.7)     | 91 (37.0)                 | 66 (26.8)      |
| TRAEs leading to chemotherapy dose reduction or interruption                  | 125 (50.8)                                  | 100 (40.7)     | 128 (52.5)                    | 104 (42.6)     | 101 (41.1)                | 83 (33.7)      |
| TRAEs leading to any discontinuation                                          | 41 (16.7)                                   | 29 (11.8)      | 30 (12.3)                     | 21 (8.6)       | 15 (6.1)                  | 10 (4.1)       |
| TRAEs leading to benmelstobart/placebo discontinuation                        | 32 (13.0)                                   | 23 (9.3)       | 15 (6.1)                      | 12 (4.9)       | 11 (4.5)                  | 8 (3.3)        |
| TRAEs leading to anlotinib/placebo discontinuation                            | 30 (12.2)                                   | 21 (8.5)       | 25 (10.2)                     | 16 (6.6)       | 11 (4.5)                  | 7 (2.8)        |
| TRAEs leading to chemotherapy discontinuation                                 | 9 (3.7)                                     | 7 (2.8)        | 10 (4.1)                      | 8 (3.3)        | 2 (0.8)                   | 2 (0.8)        |
| Benmelstobart/anlotinib-related AEs leading to discontinuation                | 21 (8.5)                                    | 14 (5.7)       | 17 (7.0)                      | 11 (4.5)       | 7 (2.8)                   | 5 (2.0)        |
| Anlotinib-related AEs leading to discontinuation                              | 3 (1.2)                                     | 1 (0.4)        | 11 (4.5)                      | 7 (2.8)        | 2 (0.8)                   | 1 (0.4)        |
| TRAEs leading to death                                                        | 11 (4.5)                                    | 11 (4.5)       | 6 (2.5)                       | 6 (2.5)        | 4 (1.6)                   | 4 (1.6)        |
| Benmelstobart/anlotinib-related AEs leading to death                          | 5 (2.0)                                     | 5 (2.0)        | 4 (1.6)                       | 4 (1.6)        | 1 (0.4)                   | 1 (0.4)        |
| Anlotinib-related AEs leading to death                                        | 0                                           | 0              | 2 (0.8)                       | 2 (0.8)        | 0                         | 0              |
| Any SAEs                                                               | 135 (54.9)                                  | 115 (46.7)     | 119 (48.8)                    | 106 (43.4)     | 101 (41.1)                | 84 (34.1)      |
| Benmelstobart/anlotinib-related SAEs                                          | 83 (33.7)                                   | 67 (27.2)      | 67 (27.5)                     | 57 (23.4)      | 43 (17.5)                 | 35 (14.2)      |
| SAEs leading to any dose reduction or interruption                            | 103 (41.9)                                  | 85 (34.6)      | 92 (37.7)                     | 79 (32.4)      | 69 (28.0)                 | 59 (24.0)      |
| SAEs leading to benmelstobart/placebo interruption                            | 80 (32.5)                                   | 61 (24.8)      | 75 (30.7)                     | 64 (26.2)      | 48 (19.5)                 | 38 (15.4)      |
| SAEs leading to anlotinib/placebo dose reduction or interruption              | 81 (32.9)                                   | 66 (26.8)      | 80 (32.8)                     | 68 (27.9)      | 47 (19.1)                 | 40 (16.3)      |
| SAEs leading to chemotherapy dose reduction or interruption                   | 72 (29.3)                                   | 60 (24.4)      | 67 (27.5)                     | 60 (24.6)      | 53 (21.5)                 | 46 (18.7)      |
| SAEs leading to any discontinuation                                           | 36 (14.6)                                   | 30 (12.2)      | 24 (9.8)                      | 20 (8.2)       | 18 (7.3)                  | 13 (5.3)       |
| SAEs leading to benmelstobart/placebo discontinuation                         | 32 (13.0)                                   | 27 (11.0)      | 19 (7.8)                      | 16 (6.6)       | 15 (6.1)                  | 13 (5.3)       |
| SAEs leading to anlotinib/placebo discontinuation                             | 28 (11.4)                                   | 23 (9.3)       | 21 (8.6)                      | 17 (7.0)       | 16 (6.5)                  | 11 (4.5)       |
| SAEs leading to chemotherapy discontinuation                                  | 10 (4.1)                                    | 10 (4.1)       | 9 (3.7)                       | 8 (3.3)        | 5 (2.0)                   | 4 (1.6)        |
| SAEs leading to death                                                         | 26 (10.6)                                   | 24 (9.8)       | 15 (6.1)                      | 15 (6.1)       | 17 (6.9)                  | 17 (6.9)       |

|                                                                   |            |           |           |          |           |          |
|-------------------------------------------------------------------|------------|-----------|-----------|----------|-----------|----------|
| Any irAEs*                                                 | 105 (42.7) | 41 (16.7) | 67 (27.5) | 20 (8.2) | 47 (19.1) | 17 (6.9) |
| irAEs leading to any dose reduction or interruption               | 47 (19.1)  | 26 (10.6) | 22 (9.0)  | 10 (4.1) | 12 (4.9)  | 8 (3.3)  |
| irAEs leading to benmelstobart/placebo interruption               | 40 (16.3)  | 20 (8.1)  | 15 (6.1)  | 6 (2.5)  | 8 (3.3)   | 6 (2.4)  |
| irAEs leading to anlotinib/placebo dose reduction or interruption | 37 (15.0)  | 24 (9.8)  | 17 (7.0)  | 9 (3.7)  | 9 (3.7)   | 8 (3.3)  |
| irAEs leading to chemotherapy dose reduction or interruption      | 20 (8.1)   | 12 (4.9)  | 7 (2.9)   | 3 (1.2)  | 11 (4.5)  | 7 (2.8)  |
| irAEs leading to any discontinuation                              | 20 (8.1)   | 15 (6.1)  | 3 (1.2)   | 2 (0.8)  | 4 (1.6)   | 3 (1.2)  |
| irAEs leading to benmelstobart/placebo discontinuation            | 17 (6.9)   | 12 (4.9)  | 2 (0.8)   | 2 (0.8)  | 3 (1.2)   | 3 (1.2)  |
| irAEs leading to anlotinib/placebo discontinuation                | 14 (5.7)   | 11 (4.5)  | 2 (0.8)   | 1 (0.4)  | 2 (0.8)   | 1 (0.4)  |
| irAEs leading to chemotherapy discontinuation                     | 1 (0.4)    | 1 (0.4)   | 0         | 0        | 1 (0.4)   | 1 (0.4)  |
| irAEs leading to death                                            | 5 (2.0)    | 5 (2.0)   | 0         | 0        | 1 (0.4)   | 1 (0.4)  |

Data are n (%). \* irAEs were assessed by investigators at each participating centers through review of patient-reported symptoms and laboratory results.

TEAEs=Treatment-emergent adverse events; TRAEs=Treatment-related adverse events; SAEs=serious adverse events; irAEs=immune-related adverse events;  
EC=Etoposide/carboplatin.

**Version History/ Revision History**

| Version number | Version date | Brief rationale and description of changes                                                                                                                                                                                                                                                                                                                                                                                                                                                                                                                                                                                                                                                                                                                                                                                                                                                                                                                                                                                                                                                                     |
|----------------|--------------|----------------------------------------------------------------------------------------------------------------------------------------------------------------------------------------------------------------------------------------------------------------------------------------------------------------------------------------------------------------------------------------------------------------------------------------------------------------------------------------------------------------------------------------------------------------------------------------------------------------------------------------------------------------------------------------------------------------------------------------------------------------------------------------------------------------------------------------------------------------------------------------------------------------------------------------------------------------------------------------------------------------------------------------------------------------------------------------------------------------|
| 1.0            | 14Aug2019    | Original version                                                                                                                                                                                                                                                                                                                                                                                                                                                                                                                                                                                                                                                                                                                                                                                                                                                                                                                                                                                                                                                                                               |
| 2.0            | 18Oct2021    | 
(1) Clarifying that the primary endpoint of PFS is assessed by IRC and the secondary endpoint of PFS is assessed by investigators;
 
(2) Myocardial damage markers, adrenocortical function, echocardiography, and lung function tests will be added during the screening period and the study to ensure the safety of the subjects;
 
(3) Clarifying the conditions for emergency unblinding;
 
(4) Addition of TQB2450 of 600 mg;
 
(5) Clarifying the maximum dose of carboplatin of 750 mg;
 
(6) Revised SAE reporting process;
 
(7) The correction of type I error in the interim analysis: considering that the O'Brien-Flemming method is used with a fixed sample size in each stage, it is not suitable for the adaptive design. Thus, the O'Brien-Flemming method is revised to the Method Based on the Sum of P-values (MSP);
 
(8) Early the futility boundary: the futility boundary b1 of added P value (MSP method);
 
(9) Sample size estimation: sample size estimation by the PROC POWER process in SAS is replaced by computer simulation.
 |
| 3.0            | 06Jun2022    | 
(1) Addition of interim analysis for OS after 70% of the planned OS events;
 
(2) The test sequence will be adjusted: the OS test (OS3) of intervention arm 1 vs. intervention arm 2; then, the OS test (OS2) of intervention arm 2 vs. control group;
                                                                                                                                                                                                                                                                                                                                                                                                                                                                                                                                                                                                                                                                                                                                                                                                                                             |

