#### 4.1 Sample Size Calculation

##### 4.1.1 Method of Sample Size Calculation

There are 3 arms in this study: Intervention arm 1 (TQB2450, Anlotinib, Carboplatin, and Etoposide); Intervention arm 2 (TQB2450 placebo, Anlotinib, Carboplatin, and Etoposide); Control arm (TQB2450 placebo, Anlotinib placebo, Carboplatin, and Etoposide). The primary efficacy endpoints of this trial are PFS and OS. In this study, a fixed-sequence test will be used for comparisons between treatment groups.

The safety analysis and re-estimation of sample size will be conducted by the Independent Data Monitoring Committee (iDMC). The re-estimation of sample size based on PFS is planned after 50% of the planned PFS events (174 cases). At the same time, a safety analysis will be performed. The interim analysis will be conducted by iDMC. One interim analysis for OS is planned for this study after 70% of the planned OS events. If expected efficacy is observed, early declaration of the study due to efficacy would be considered. The interim analysis will be conducted by iDMC.

The previous study showed that the median OS and PFS in the control arm were 10 and 4 months, respectively [5]. Patients were enrolled within a 12-month accrual period with an 18-month follow-up and were randomly assigned (1:1:1) to three groups. The power was 85% with a type I error rate of 0.050 and a dropout incidence of 10%. The type I error rate in the interim analysis for PFS will be controlled by the Method Based on the Sum of P-values (MSP). The initial sample size in this study will be estimated based on PFS using a computer simulation program.

##### 4.1.2 Sample Size Estimation in the Intervention Arm 1

Assuming that the HR for PFS in the intervention arm 1 compared with the control arm is 0.6, the hazard rate in the intervention arm 1 is 0.1040, and that in the control arm is 0.1733 along with exponential distribution. Approximately 165 PFS events are expected if 174 patients are enrolled. A total of 194 patients are recruited and randomly assigned (1:1) to intervention arm 1 and control arm, considering an approximate dropout incidence of 10%. The interim analysis will be conducted when the planned PFS events are ~83. The final analysis will be performed after ~165 of the planned

PFS events.

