### 13.2.2 Size of a Test

#### (1) Type I error control in the multiple-group comparison

There are 3 arms in this trial:

Intervention arm 1: TQB2450, Anlotinib, Carboplatin, and Etoposide

Intervention arm 2: TQB2450 placebo, Anlotinib, Carboplatin, and Etoposide

Control arm: TQB2450 placebo, Anlotinib placebo, Carboplatin, and Etoposide

The primary efficacy endpoints of this trial are PFS and OS. In this trial, a fixed-sequence test will be used for comparisons between treatment groups:

- a) The PFS between intervention arm 1 and the control arm (PFS1) will be first tested with the two-sided significance level of 0.05 (one-side, 0.025). If PFS1 is statistically significant, the OS between intervention arm 1 and the control arm (OS1) will be then tested.
- b) If OS1 is statistically significant, the PFS between intervention arm 2 and the control arm (PFS2) will be tested.
- c) If PFS2 is statistically significant, the OS between intervention arm 1 and intervention arm 2 (OS3) will be then tested.
- d) If OS3 is statistically significant, the OS between intervention arm 2 and the control arm (OS2) will be tested.

The overall significance level is set as 0.05 at two-side (one-side, 0.025). Familywise error rate (FWER) will be controlled by the fixed order test when each hypothesis presupposes the rejection of all previous tests.

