#### (2) Type I error control for the re-estimation of sample size based on PFS

The safety analysis, re-estimation of sample size, and efficacy analysis will be conducted by the iDMC. The re-estimation of sample size based on PFS is planned after 50% of the planned PFS events (174 cases). At the same time, a safety analysis will be performed. The interim analysis will be conducted by iDMC.

The non-blind re-estimation of sample size is a procedure with multiple tests, with a concern on data dependency in different stages, which would increase the inflation of the type I error rate. To address this problem, P values in two stages will be combined using the MSP.

According to the preliminary test, in the PFS interim analysis based on the re-estimation of sample size, the one-side significance level is set as  $\alpha_1=0.005$ , and the futility boundary is set as  $b_1=0.45$  in the first stage; the one-side significance level is set as  $\alpha_2=0.2050$  in the secondary stage. No early discontinuation of the study due to PFS efficacy would be considered.

- Either  $P_1 \leq \alpha_1$  or  $P_1 > \alpha_1$ , once  $P_1 \leq b_1$ , the trial will continue to the second stage, without early discontinuation due to PFS efficacy;

- If  $P_1 > b_1$ , the trial will terminate early for futility;
- If the trial could proceed into the second stage,  $P_1 + P_2 \leq \alpha_2$  [that is, adjust P value =  $\alpha_1 + (P_1 + P_2)(b_1 - \alpha_1) - 1/2 (b_1^2 - \alpha_1^2) \leq 0.025$ ], the between-group difference in PFS will be considered as statistically significant.

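### The sum-of-P-values rule for PFS is valid and delivers the planned 85% power, but a pre-weighted inverse-normal combination would give more power on the gatekeeping PFS tests with the same type I error protection

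*Protocol*

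**What the plan says.** Item (7) of the version 2.0 entry in the Protocol's revision history records that "the O'Brien-Flemming method is revised to the Method Based on the Sum of P-values (MSP"). It gives the only reason for the method: O'Brien-Fleming presumes fixed stage sizes and so does not fit an adaptive design. The choice is operative in two places. Section 4.1.1 states: "The type I error rate in the interim analysis for PFS will be controlled by the Method Based on the Sum of P-values (MSP"). Section 13.2.2(2), after noting that unblinded sample-size re-estimation can inflate type I error, states: "To address this problem, P values in two stages will be combined using the MSP".

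Section 13.2.2(2) sets alpha1 = 0.005 and a futility bound b1 = 0.45 on the stage-1 P value, and a bound of 0.2050 on P1+P2. It adds: "No early discontinuation of the study due to PFS efficacy would be considered". If P1 <= 0.45 the trial goes on to stage 2 whether or not P1 is below alpha1, and significance is then declared on the sum.

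Section 13.2.2(1) tests PFS1 first, "with the two-sided significance level of 0.05 (one-side, 0.025"). The sequence is PFS1, OS1, PFS2, OS3, OS2. Sections 4.1.2 and 4.1.3 plan 165 events at HR 0.60 and 231 events at HR 0.65, with 85% power (4.1.1). Section 4.1.4 places the PFS looks at 174 and 347 events. Section 4.2 ties the final PFS analysis to the OS interim, at whichever comes later.

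**The concern.** A possible change of stage-2 size calls for a combination of independent stage-wise P values, but it does not call for their sum. The sum has two costs. It caps P2 at 0.205 even when stage 1 is overwhelming. And the bound 0.2050 uses the full 0.025 only if P1 <= 0.005 counts as a success by itself, which the stated rule does not allow.

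PFS1 is the gate to every later test, and PFS2 is the gate to OS3 and OS2, so PFS power also limits the OS claims. The sum rule can also disagree with the stratified log-rank P value and the Cox confidence interval that section 13.4.1 reports beside it.

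**Working it through.** **Inputs.** HR 0.60 with 165 events (4.1.2), HR 0.65 with 231 events (4.1.3), interim at half the events, 1:1 allocation, b1 = 0.45 and bound 0.2050 (13.2.2(2)), one-sided 0.025 (13.2.2(1)). The explicit bound on P1+P2 is taken as the rule.

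**Drift.** With d_s events in a stage, Z has mean |ln HR| x sqrt(d_s/4) and variance 1.
- HR 0.60: 0.5108 x sqrt(82.5/4) = 2.320 per stage.
- HR 0.65: 0.4308 x sqrt(115.5/4) = 2.315 per stage.

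**Step 1: reproduce the plan.** Integrating Pr(P1+P2 <= 0.2050) over two independent stages gives 84.6% at 165 events and 84.4% at 231. Exactly 85% needs 167 and 235. A single-look log-rank test would need only 138 and 194, so the planned counts already include the cost of the sum.

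**Step 2: size.**
- As written: 0.2050^2/2 = 0.0210.
- With P1 <= 0.005 also a claim: 0.005 + (0.2050 - 0.005)^2/2 = 0.025. This is how the bound uses the full alpha.
- A sum rule using all of 0.025 without that claim needs c^2/2 = 0.025, so c = 0.2236.
- Equal-weight inverse-normal, (Z1+Z2)/sqrt(2) >= 1.96 and P1 <= 0.45: 0.0245.
- Simulated under unblinded re-estimation with an assumed rule (conditional power 85%, various caps on the increase): inverse-normal 0.0244 to 0.0248, sum rule about 0.021.

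**Step 3: power at the per-comparison event counts.**

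| Rule | HR 0.60, 165 events | HR 0.65, 231 events | Events for 85% |
|---|---|---|---|
| Sum, bound 0.2050 | 84.6% | 84.4% | 167 / 235 |
| Sum, bound 0.2236 | 86.2% | 86.1% | 159 / 223 |
| Inverse-normal, b1 = 0.45 | 90.3% | 90.2% | 139 / 196 |

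For PFS1, 86.2 - 84.6 = 1.6 points is unspent alpha and 90.3 - 86.2 = 4.1 points is the sum itself. PFS2 splits almost identically (1.7 and 4.1).

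**Step 4: power when PFS would actually be tested.** Assumptions: exponential PFS at the plan's hazards, 246 patients per arm, uniform 12-month accrual, no dropout. For the OS timing, control median 10 months and HRs 0.70 and 0.72.
- 347 pooled PFS events: about 240 in arm 1 plus control and 245 in arm 2 plus control. PFS1 is 94.5% v 97.5% (3.0 points); PFS2 is 86.4% v 91.8% (5.4 points).
- 348 deaths (OS interim): about 554 pooled PFS events. PFS1 has about 121 stage-1 and 257 stage-2 events. With weights matched to the split, PFS1 is 97.6% v 99.5% (about 2 points) and PFS2 is 93.5% v 97.9% (4.4 points).

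**Step 5: where the rules differ** (equal weights; inverse-normal needs Z2 >= 2.772 - Z1).
- P1 = 0.001 (Z1 = 3.09): the sum needs P2 <= 0.204, Z2 >= 0.83; inverse-normal needs Z2 >= -0.32.
- P1 = 0.05 (Z1 = 1.645): the sum needs P2 <= 0.155; inverse-normal needs P2 <= 0.130.
- P1 = 0.10 (Z1 = 1.282): the sum needs P2 <= 0.105; inverse-normal needs P2 <= 0.068.
- P1 = 0.17 (Z1 = 0.954): both need P2 of about 0.035.

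At HR 0.60 and 165 events, about 6.9% of simulated trials reach an ordinary log-rank Z >= 1.96 yet fail the sum rule; about 0.8% do the reverse.

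**The case against.** The strongest reply is that nothing here is wrong. The method and its bounds are pre-specified, type I error is below 0.025, and the event counts already pay for the sum, so the stated 85% is met. That stands. A reader might infer that the rule is invalid or the trial underpowered for PFS; the documents support neither.

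A reader might also take the gap of about 6 points at 165 and 231 events as the loss in the trial. Those counts size each comparison alone, whereas 4.1.4 and 4.2 place the final PFS analysis later, where the gap for PFS1 is 2 to 3 points. Nor is the whole gap due to the sum, since about 1.6 points is unused alpha. If P1 <= 0.005 were read as a PFS claim, the gap at 165 events would fall to 90.3 - 87.3 = 3.0 points. But the stated success rule does not include that claim, and it would need only about 154 events, not 165.

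Requiring a supportive second stage is a legitimate preference. Stage 1 is not thrown away, because P1 enters the sum, and the inverse-normal rule can succeed with a flat or slightly adverse stage 2 when stage 1 is very strong. For P1 of about 0.05 to 0.17 the sum rule is the slightly easier one.

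Two further inferences fail. Fewer PFS events would not mean fewer patients: 738 = 1.5 x 492, and 492 comes from the OS calculation in 4.1.3. And any power figure under re-estimation would rest on an assumed rule, because 4.2 leaves the real one to the iDMC guidelines; none is relied on here.

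**Conclusion.** The point holds as an efficiency improvement, to be considered, and not as a correction of an error. The plan's only stated reason for the method does not require a sum. A combination with fixed weights gives the same protection, uses nearly all of the alpha (0.0245 against 0.0210), and gains about 3 points for PFS1 and 5.4 for PFS2 at 347 pooled events, or about 2 and 4 to 4.5 if PFS waits for the OS interim. The gain is therefore modest at the first gate and larger at PFS2, which opens OS3 and OS2. The figures rest on proportional hazards, exponential PFS at the plan's HRs, 12-month uniform accrual and no change in sample size.

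**What to change.** In 13.2.2(2), and by reference in 4.1.1, replace the sum rule by sqrt(w1) x Z1 + sqrt(1 - w1) x Z2 >= 1.96. Fix w1 in advance, for each comparison, at the planned stage-1 share of its events. Take Z1 and Z2 from independent stage-wise increments of the stratified log-rank statistic. Keep futility at P1 > b1 and keep no early PFS efficacy stop. Restate PFS power at the events actually planned for each comparison, which means settling whether the final PFS analysis falls at 347 events or at the OS interim: under the assumptions above, w1 for PFS1 would be about 121/240 = 0.50 or 121/378 = 0.32.

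The decision then matches the ordinary log-rank test only if the observed stage split equals w1, so the text should not promise more.

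The cost is wording and a re-run of the sizing program, with no added patients or procedures. The change is acceptable only before any unblinded PFS interim; after that, the written rule should stand.
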